### Participant retention and follow-up

Researchers will follow up twice by phone and/or email with participants who register to attend an orientation session, but do not attend, in order to encourage their participation in the trial. Participants will be sent two email reminders to complete the T2 and T3 questionnaires within 1 week of being sent these questionnaire links. The questionnaire links expire after 1 week. Participants will be provided with online vouchers as reimbursement for their time at the completion of each data collection point: T1 = AUD30; T2 = AUD30; T3 = AUD40; Total = AUD100.

### Sample size and power analysis

The sample size is calculated to detect a 0.25 standardised difference in mean on the GHSQ-Self score between the intervention and control group (90% power, 2-sided 5% significance level), assuming a correlation of 0.67 between T1 and T2 scores. This sample size of 446 participants also allows for 20% loss to follow-up. We have chosen a relatively small effect size given the universal nature of the intervention, where we would aim to create change by producing a small effect on a large number of men, and given that we are measuring intentions to seek help as the primary outcome, rather than actual help-seeking behaviour. Intentions was chosen over behaviour as the primary outcome given the small amount of time between T1 and T2 in which participants would have the opportunity to seek help as the need arose.

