## Methods

### Study design

This is a single-blinded, two-arm RCT comparing the effects of an intervention video against a control video. We plan to recruit 446 adult Australian men to be randomised, with a 1:1 allocation (223 participants per arm).

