### Statistical analyses

#### Primary outcomes

Analyses of continuous outcomes will be undertaken on an intent-to-treat basis, including all participants who have been randomised, regardless of their actual receipt of the intervention or withdrawal from the study. Mixed-model repeated measures (MMRM) analyses will be used because of the ability of this approach to include participants with missing data. The model will include factors of intervention arm, occasion of measurement (T1, T2), and their interaction. The effectiveness of the intervention will be assessed by a planned comparison of the difference between groups in change of the primary outcome variable from T1 to T2. An unstructured residual variance-covariance matrix will accommodate within-participant dependency. Tests of significance will use degrees of freedom adjusted using the Kenward-Roger method based on the observed information matrix. If necessary, transformation of the outcome variable will be undertaken to ensure distributional assumptions of the model are met.

Analysis of primary outcomes and some secondary outcomes will take place when all T2 post-intervention data have been collected, but before T3 follow-up data have been collected. This analysis will assess the effectiveness of the intervention from T1 to T2 on increasing participants’ intentions to seek help for mental health difficulties (primary outcome), and intentions to encourage other men to seek help and self-reliance (secondary outcomes).

At this time, we will assess whether there is evidence of a lack of net harm associated with viewing the intervention video. Doing this will allow us to inform the production company tasked with releasing the video into the public domain and promoting public access to the video whether they can release the film in the following month. This release will be dependent on the analysis of primary outcomes showing evidence of lack of net harm. Lack of net harm will be indicated by the lower confidence interval of the mean GHSQ-Self score in the intervention condition post intervention being no lower than that in the control condition, adjusting for any baseline differences. The parameters will be estimated within the framework of the models used to assess the effectiveness of the intervention (i.e. we will use an MMRM to obtain the estimated means and their confidence intervals).

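### 446 participants give 90% power only with no loss; after the stated 20% loss, the planned change comparison has about 84%

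*Protocol article*

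**What the plan says.** The section on sample size and power gives every input. The target is set out as follows: "The sample size is calculated to detect a 0.25 standardised difference in mean on the GHSQ-Self score between the intervention and control group", with "90% power, 2-sided 5% significance level" and "assuming a correlation of 0.67 between T1 and T2 scores". It then states: "This sample size of 446 participants also allows for 20% loss to follow-up". The Study design section splits the 446 randomised men equally, 223 to each arm.

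The Primary outcomes part of the statistical analyses fixes the test. It is a mixed model for repeated measures with an unstructured covariance: "The model will include factors of intervention arm, occasion of measurement (T1, T2), and their interaction". Effectiveness is judged by a "planned comparison of the difference between groups in change of the primary outcome variable from T1 to T2". The Discussion confirms that the primary assessment contrasts the arms on change. T1 is therefore one of the responses in the model. For the efficacy test, no baseline covariate is named and the arms' baseline means are not constrained to be equal.

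**The concern.** With complete data at two occasions, the arm-by-occasion contrast in this model is the between-arm difference in mean change, so its variance is governed by 2(1 − ρ). With the protocol's own inputs, that variance leads to 223 per arm before any allowance for loss. The number randomised should exceed the number of completers needed, but here the two are equal.

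What is at stake is the false-negative risk on the single primary question. The protocol deliberately targets a small effect, and a null result would be read against the stated 90%. Under the protocol's own attrition assumption the type II error is about 16%, not 10%. The type I error, the estimate and its confidence interval remain valid.

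**Working it through.** **Inputs.** d = 0.25 in units of the raw-score SD, ρ = 0.67, two-sided 5% (z = 1.960), 90% power (z = 1.2816) and 20% loss, all from the sample size section; N = 223 per arm from Study design.

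**Step 1: size before using the correlation.** 2 × (1.960 + 1.2816)² / 0.25² = 336.2 per arm.

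**Step 2: reproduce 446.** Two routes reach it.

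- *Change contrast, no loss.* 336.2 × 2(1 − 0.67) = 336.2 × 0.66 = 221.9, so 222 per arm. With the t distribution it is 223 per arm, or 446 in total. Power at 223 complete pairs per arm is 90.1% (normal) or 90.0% (t).
- *Baseline-adjusted comparison of T2 scores.* 336.2 × (1 − 0.67²) = 336.2 × 0.5511 = 185.3, so about 186 per arm. Multiplying by 1.2 gives 185.3 × 1.2 = 222.4, so 223 per arm, or 446. Allowing for 20% loss requires division instead: 185.3 / 0.8 = 231.6, so 232 per arm, or 464 (466 if 185.3 is rounded up to 186 before dividing).

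Using T2 scores without the correlation needs 337 per arm and does not reproduce 446.

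**Step 3: power after 20% loss at T2.** Observed at T2: m = 223 × 0.8 = 178.4 per arm.

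- *Planned mixed model, keeping the T1 data of those lost.* Variance per arm = (1 − ρ²)/m + (1 − ρ)²/N = 0.5511/178.4 + 0.1089/223 = 0.003089 + 0.000488 = 0.003577. SE = √(2 × 0.003577) = 0.0846. Power = Φ(0.25/0.0846 − 1.960) = 84.0%. A simulation of 20,000 trials gave 84.1%.
- *Change score in completers only.* SE = √(2 × 0.66/178.4) = 0.0860. Power = 82.8%.
- *Baseline-adjusted or constrained-baseline contrast.* SE = √(2 × 0.5511/178.4) = 0.0786. Power = 88.9%.

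**Step 4: detectable effect under the planned model.** (1.960 + 1.2816) × 0.0846 = 0.274 SD.

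**Step 5: total that would give 90% with 20% loss.**

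| Analysis | Per arm | Total |
|---|---|---|
| Planned mixed model | 269 | 538 |
| Completers' change score (223/0.8) | 279 | 558 |
| Baseline-adjusted (185.3/0.8) | 232 | 464 |

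**Step 6: dependence on the loss.** At 223 randomised per arm, power of the planned contrast is 90.1% with no loss, 88.9% at 5%, 87.5% at 10%, 85.9% at 15% and 84.0% at 20%.

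**The case against.** The strongest reply is that 446 may have come from the baseline-adjusted route. The target is worded as a difference in scores rather than in change, and that route does contain an allowance for loss, as the protocol says. The slip would then be multiplying by 1.2 instead of dividing by 0.8, which costs about one point of power (88.9% against 90%). The rest of the gap would be a mismatch between the sizing method and the analysis model. This is fair as to origin: the protocol does not show how 446 was obtained. It does not rescue the claim. Power after 20% loss stays below 90% on that route too, and it is not the contrast the protocol specifies. Baseline adjustment is mentioned only for the lack-of-net-harm criterion.

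Two further points limit the size of the problem. First, T2 falls one week after T1, with reminders and a voucher, so loss by T2 may be well under 20%; at 10% the planned contrast has 87.5%. That stands as a comment on likely power, but the sentence under review claims 90% with 20% loss. Second, the social support item is to be used in analyses of the GHSQ-Self and might add precision. No gain is stated, and the item is not in the primary model as described, so it cannot support the 90%.

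The mixed model's use of incomplete records is already credited in the 84.0%; it adds about one point over completers only.

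**Conclusion.** The statement is wrong as written. For the analysis the protocol specifies, 446 gives 90% power with complete T2 data and about 84% with 20% missing at T2, when the detectable effect is 0.274 SD rather than 0.25. If a baseline-adjusted contrast was intended, power with that loss is about 89%. Neither calculation that reproduces 446 delivers 90% after 20% loss.

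These figures assume equal SDs at T1 and T2, equal loss in both arms occurring entirely at T2 and at random, the protocol's d and ρ, and no gain from other covariates.

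**What to change.** Replace the sentence on loss to follow-up with a statement such as:

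*With 446 men randomised, the trial has 90% power to detect 0.25 SD if all provide T2 data. If 20% do not, power is about 84% for the unconstrained difference-in-change contrast and about 89% for a contrast adjusted for, or constrained at, baseline.*

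If the baseline-adjusted contrast is the one intended, say so in the Primary outcomes section before unblinding, so that the sizing and the model agree. That alone recovers most of the shortfall.

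The cost is one sentence and a slightly less favourable power figure. No extra recruitment is asked for; the Trial status section reports that recruitment had already begun.

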### Data collection and management

Data will be collected via an online system administered by the external data management company, Strategic Data Ltd. Data will be entered directly by participants into the online questionnaires, minimising the chances of missing data and data entry mistakes. With the exception of some free-text response questions, questionnaire responses will be restricted to those values that are valid responses for each question (e.g. maximum 28 days if questions ask ‘on how many days in the last four weeks…’). Warning messages will be triggered if invalid entries are entered or if participants have not answered mandatory questions.

Strategic Data will set up and host the online forms and technology to collect the participant data. The hosting is in a highly secure Australian-based environment. The participant’s access is password protected and locked upon completion of each survey. This means that if anyone accesses the participant’s username and password once their participation has ended, their record will not be accessible. This further will further minimise the risk of inappropriate access.

Once the data collection is complete and upon request from one of the two lead investigators, Strategic Data will supply a final encrypted version of the dataset for 5-year storage at University. Respondent questionnaire data and identifying information will be sent separately and will be encrypted and password-protected. Strategic Data will then delete all respondent data from its active systems, leaving only backups which will be deleted over time in the normal course of backup protocols.

The trial manager will manage the data at the University of Melbourne. Online survey data will be password-protected, and exported data files will be stored on the university server in a password-protected folder to which only the researchers employed on this trial will have access. Upon completion of the trial, all data and related information will be stored on the secure university server. This information will not be deleted until any continued interest in the information ceases or until at least 5 years following the final publication relating to that research.

### Confidentiality

Strategic Data will have participants’ identifying data for the purpose of sending personalised email invitations and reminders. They will match the data over the three data collection points by allocating participants a unique identifier and will store identifying information separately from the questionnaire data. The only time participants’ identifying data and questionnaire data will be linked will be if the participant scores above the cut-off for suicide risk. In this instance, Strategic Data will supply the researchers and the study psychologist the following data for the purpose of following up the participant: the participants’ name and phone number, the name and contact number of their nominated emergency contact person, their total score on the screening questionnaire (DSI-SS), and their responses to the DSI-SS items. At the end of the data collection period, Strategic Data will supply our research team with both the database containing both the participants’ details and another database containing the questionnaire data. These will be sent and stored separately. These databases will then be stored on the University’s secure server.

### Statistical analyses

#### Primary outcomes

Analyses of continuous outcomes will be undertaken on an intent-to-treat basis, including all participants who have been randomised, regardless of their actual receipt of the intervention or withdrawal from the study. Mixed-model repeated measures (MMRM) analyses will be used because of the ability of this approach to include participants with missing data. The model will include factors of intervention arm, occasion of measurement (T1, T2), and their interaction. The effectiveness of the intervention will be assessed by a planned comparison of the difference between groups in change of the primary outcome variable from T1 to T2. An unstructured residual variance-covariance matrix will accommodate within-participant dependency. Tests of significance will use degrees of freedom adjusted using the Kenward-Roger method based on the observed information matrix. If necessary, transformation of the outcome variable will be undertaken to ensure distributional assumptions of the model are met.

Analysis of primary outcomes and some secondary outcomes will take place when all T2 post-intervention data have been collected, but before T3 follow-up data have been collected. This analysis will assess the effectiveness of the intervention from T1 to T2 on increasing participants’ intentions to seek help for mental health difficulties (primary outcome), and intentions to encourage other men to seek help and self-reliance (secondary outcomes).

At this time, we will assess whether there is evidence of a lack of net harm associated with viewing the intervention video. Doing this will allow us to inform the production company tasked with releasing the video into the public domain and promoting public access to the video whether they can release the film in the following month. This release will be dependent on the analysis of primary outcomes showing evidence of lack of net harm. Lack of net harm will be indicated by the lower confidence interval of the mean GHSQ-Self score in the intervention condition post intervention being no lower than that in the control condition, adjusting for any baseline differences. The parameters will be estimated within the framework of the models used to assess the effectiveness of the intervention (i.e. we will use an MMRM to obtain the estimated means and their confidence intervals).

We have chosen the change in help-seeking intentions between T1 and T2 as our primary outcome for two main reasons. First, we expect that if there is an effect of this short intervention video, it will be immediate. We are encouraging men to seek help for mental health difficulties before they escalate. These sorts of difficulties are extremely common, and the help-seeking message is therefore likely to be immediately salient to most participants. We recognise that while intentions to seek help can change immediately, actual help-seeking may take longer. Therefore, we will assess help-seeking behaviour as a secondary outcome at T3 (1-month after baseline), as well as whether any increase in help-seeking intentions has been retained. Second, in the context of our collaboration with our film and advertising colleagues, we have created a broader campaign within which this video is at the core. The broad campaign will promote the video within the context of a range of other campaign materials promoting help-seeking. Within this trial, we want to be sure that the video does no harm to participants and ideally has a positive impact, but we also anticipate that by itself, this short video would be likely to have a short, sharp impact, while the broader campaign will have a greater, more lasting impact. We will do further empirical evaluation to test the impact of the broader campaign once it has been released. Therefore, the findings of this trial form a broader assessment of the campaign impacts that focus purely on the shorter-term effects of the video viewing.

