However, a 3-h documentary requires significant investment both in terms of production costs and viewing time. Through this RCT, we will test whether a similar message to that promoted in the 3-h ‘Man Up’ documentary, encouraging men to seek help when they are experiencing mental health difficulties, can be effective when delivered through a much shorter video. In this RCT, we will test whether a 4-min video is similarly effective in promoting help-seeking among Australian men. If this video is shown to have no net negative effect on help-seeking, this video will be publicly released. The release of the video will be supported through a comprehensive media campaign aimed at promoting viewing of the video and for viewers to visit a purpose-designed website, which will house help-seeking and help-offering information, as well as other supporting videos and content.

Data assessing men’s help-seeking intentions, intentions to encourage other men to seek help, self-reliance, depression symptoms, and opinions regarding the allocated video will be collected across three timepoints: baseline (T1), post-intervention (T2—1 week after baseline), and 4-week follow-up (T3—4 weeks after T2). Participants will view the video between T1 and T2.

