##### Intervention

The intervention is a music video of approximately 4-min length created specifically for this study. It features a large group of diverse men singing a song in a community town hall. The song’s lyrics relate to the need for men to talk to others when experiencing mental health difficulties and to encourage others to do the same. The ‘call to action’ at the end of the video is ‘When the going gets tough. Get Talking’, and then there is a link to a website, which will provide links to further mental health support. This website will not be live during the trial to ensure that we can isolate any effects of the video from any effects of additional actions that might take place after participants watch the video.

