### Participant timeline

After registering their interest in participation, participants will attend an online information session. After consenting, participants will immediately be given a link to complete the T1 questionnaire, which will include questions about socio-demographics, suicide risk, help-seeking intentions, intentions to encourage other males to seek help, male depression symptoms, self-reliance, health service use, and social support. Following completion of the T1 questionnaire, participants will be randomly assigned to intervention or control groups by the independent data management contractor. Immediately after randomisation, Strategic Data will email participants a link to their allocated online video (intervention or control); they will also receive a reminder to watch the video at day 3. They will be sent the video link again on day 7, along with the link to the T2 questionnaire. The T2 questionnaire will include questions about help-seeking intentions, intentions to encourage other males to seek help, self-reliance, social support, and feedback on the video. If participants do not view the video within 1 week of receiving the link or do not complete the T1 questionnaire, two reminder emails will be sent 10 and 12 days after T1. The link will expire after 1 week and participants will no longer be able to complete the T2 questionnaire. One month after T2, participants will be emailed the T3 questionnaire, which replicates the T1 questionnaire with the exceptions that it also includes questions about the effects of viewing the allocated video and does not include the DSI-SS. Participants will receive two reminders 3 and 5 days after the initial T3 email is sent. The link will expire after 1 week and participants will no longer be able to complete the T3 questionnaire. All participants who complete the T1 questionnaire will proceed to the T3 questionnaire, regardless of whether they complete the T2 questionnaire or watch their allocated video. See Fig. 1 for the timeline for the trial and Table 1 for the schedule of assessments.

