**Fig. 1 Fig1:**
[figure not shown]
Timeline for the trial. *Note:* DSI-SS, Depression Symptom Inventory—Suicidality Subscale [12]. See Table 1 for further information about T1, T2, and T3 questionnaires and timing

**Table 1 Tab1:** Schedule of assessments

Variable	Measure	Timeline		
		T1	T2	T3
*Screening measure*				
Suicide risk	Depression Symptom Inventory—Suicidality Subscale [12]	X		
*Primary outcome measure*				
Help-seeking intentions	General Help-Seeking Questionnaire—Self [13]	X	X	X
*Secondary outcome measures*				
Intentions to encourage other males to seek help	General Help-Seeking Questionnaire—Other [13]	X	X	X
Self-reliance	Conformity to Masculine Norms Inventory 30—Self-reliance subscale [14]	X	X	X
Male depression symptoms	Male Depression Risk Scale-7 [15]	X		X
Health service use	Health Service Use Questionnaire	X		X
*Other measures*				
Socio-demographics	Information about age, postcode, country of birth, language, marital status, current student, highest education, and employment	X		
Social support question	Information about the number of close friends and close relatives	X	X	X
Feedback on video	Information about video enjoyment, likeability, take-home message, degree of intended sharing with others, and belief about impact		X	
Effects of viewing the video	Information about life changes and time spent with friends			X

*Note.* T1, the T1 questionnaire is completed in the online information session; T2, the T2 questionnaire becomes available 7 days after completion of the T1 questionnaire and the survey expires after 1 week; T3, the T3 questionnaire is made available 4 weeks after the T2 questionnaire is completed or expires. The survey link expires after 1 week

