## Dissemination

We will prepare a lay summary of the outcomes of the RCT and will email it to all participants who indicate on the consent form that they are interested in receiving these results. We will publish several peer-reviewed journal articles and deliver presentations at national and international conferences. We will also deliver other presentations about the trial to other mental health and suicide prevention researchers and professionals. If the intervention video is shown to have no net negative effect on help-seeking, it will be publicly released and its release will be supported by a media campaign that will include the video on a project website with complementary content, social media dissemination, media interviews, and other strategies for increasing public interaction with the video.

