## Trial status

This RCT has been the Australian New Zealand Clinical Trials Registry (No. 12621001008819) [9]. Recruitment commenced on 16 August 2021 and will end on 2 October 2021. Data collection will continue until the end of November 2021.

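### The film's release is tied only to lack of net harm at T2 and not to the close of T3, so late recruits, including controls, could meet it before they answer T3

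*Protocol article*

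**What the plan says.** The Primary outcomes section places the T2 analysis after all T2 data are in and before T3 data have been collected. The result is then used to tell the company responsible for releasing the film and "promoting public access to the video whether they can release the film in the following month". The condition is: "This release will be dependent on the analysis of primary outcomes showing evidence of lack of net harm". The Abstract, Background and Dissemination sections give the same condition and add no other.

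The release is not meant to be quiet. Background says: "The release of the video will be supported through a comprehensive media campaign". Dissemination adds that "its release will be supported by a media campaign that will include the video on a project website with complementary content", together with social media and media interviews.

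The one related safeguard is in the Intervention section and concerns the website linked from the end of the video: "This website will not be live during the trial to ensure that we can isolate any effects of the video".

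On timing, the note to Table 1 says "the T3 questionnaire is made available 4 weeks after the T2 questionnaire is completed or expires", with a link life of one week. Participant timeline instead has T3 emailed one month after T2. It also says: "All participants who complete the T1 questionnaire will proceed to the T3 questionnaire, regardless of whether they complete the T2 questionnaire". Trial status gives the calendar: "Recruitment commenced on 16 August 2021 and will end on 2 October 2021. Data collection will continue until the end of November 2021".

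**The concern.** The T1-to-T3 changes in help-seeking intentions, encouragement of others, self-reliance and male depression symptoms are secondary outcomes. T3 is also where the plan looks for actual help-seeking, and its service-use data feed the cost-effectiveness analysis. All of these compare the allocated video with the control video.

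A control who sees the released film before answering T3 has received the intervention, and the contrast moves towards no retained effect. An intervention participant may see the film again, with the campaign and website around it, which could push the other way. Dilution is the more likely net result. Release would also undercut the plan to keep participants unaware of the two videos until T3, and would colour the T3 question on believed allocation.

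Contact is plausible. Recruitment runs through partners' social media and the networks of the film and advertising colleagues, and the release uses social media as well. The T3 questions described under Other measures do not include seeing the film outside the trial, so contamination could go unnoticed.

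**Working it through.** **Inputs.** T1 runs from 16 August to 2 October 2021, which is 48 days (Trial status). T2 opens at T1 + 7 days and expires at T1 + 14 (Table 1). T3 opens 28 days after T2 is completed or expires (Table 1), or one month after T2 (Participant timeline), and closes 7 days later.

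**Last participant, T1 on 2 October.**
- T2 opens 9 October and expires 16 October.
- Four-week rule: T3 opens at T1 + 35 to T1 + 42, i.e. 6-13 November, and closes at T1 + 42 to T1 + 49, i.e. 13-20 November.
- Calendar month: T2 expiring on 16 October gives T3 opening 16 November and closing 23 November, i.e. T1 + 52.

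Both agree with the stated end of data collection, the end of November.

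**When release is allowed.** All T2 data can be in by 16 October. If the analysis is finished in October, the month that follows is either a month from that date (16 October to 16 November at the earliest) or the calendar month 1-30 November. Both overlap open T3 windows. If the analysis is finished in November, the next calendar month is December and there is no overlap.

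**Share of participants at risk.** The document gives no release date, so the dates below are illustrations. I assume even recruitment over the 48 days and the four-week rule. Low ends take T2 as completed on day 7, high ends as expired on day 14.

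| Release | T3 link not yet opened | T3 link not yet closed |
|---|---|---|
| 1 November | 6-13 of 48 days = 12.5-27.1% | 13-20 of 48 = 27.1-41.7% |
| 8 November | 0-6 of 48 = 0-12.5% | 6-13 of 48 = 12.5-27.1% |
| 16 November | 0 | 0-5 of 48 = 0-10.4% |
| 21 November | 0 | 0 |

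The right-hand column is an upper limit, since some will already have answered. If 80% complete T2 evenly over days 7-14 and 20% never do, the not-yet-opened shares are 21.3%, 6.9% and 0% for the first three dates.

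The calendar-month reading moves these later. For a 21 November release, T2 links expiring on 14-16 October (T1 on 30 September to 2 October) would still have T3 open: 3 of 48 days, 6%. Overlap then ends on 24 November.

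**Dilution.** If a share *s* of controls has T3 unopened at release, and a fraction *e* of them see the film and gain its full effect, the T3 contrast shrinks by *s* × *e*. The document gives no value for *e*; I assume 0.10 to 0.50. For a 1 November release under the four-week rule:
- low: 0.125 × 0.10 = 0.013
- high: 0.27 × 0.50 = 0.135
- mixed case at low exposure: 0.213 × 0.10 = 0.021

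For 8 November, the mixed case at low exposure gives 0.069 × 0.10 = 0.007.

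**The case against.** The best defence reads the sections together. The website is to stay offline during the trial, and the trial includes T3: Participant selection and Provisions for post-trial care describe the same four weeks of psychologist access as running from completion of T3 and from completion of the trial. The video ends with a link to that website, and the release is to bring viewers to a website that hosts the film. On that reading a release as described cannot happen before T3 ends. The release wording is also a permission and fixes no date.

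Much of this stands. A reader might infer that the plan schedules a public release during T3, or that controls will be contaminated. The document supports neither: overlap depends on when the analysis finishes and when the company acts, and release from late November avoids it. What does not stand is that the matter is settled. The safeguard names the website and not the film, and the rule given to the production company contains no T3 condition. The reason for the safeguard, isolating the video's effect, applies with more force to the film itself. This is a stated rule that is badly fixed, so the missing condition cannot be put down to the condensed form of an article.

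Two further objections also hold. The 1-14% figure rests on assumed exposure at one early date. And 20 November is the last close only under the four-week rule.

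**Conclusion.** The point holds as an unresolved tension between the release rule and the website safeguard. Following the rule as written could expose late recruits in both arms to the film before T3. The latest T3 close is 20 November 2021 under Table 1, or about 23 November under the one-month wording.

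The damage is confined to the secondary T1-to-T3 contrasts, T3 service use and the concealment that should last until T3. It most likely acts towards the null. Its size is unknown and probably modest, because only later recruits are at risk and many of them may never meet the film. The calendar shares assume even recruitment, with the last T1 on 2 October; the dilution range also assumes the exposure fraction and a full effect in exposed controls.

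It would be wrong to infer that the trial's main result is threatened. The T1-to-T2 primary outcome and the harm decision are made on data collected before any release.

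**What to change.** Keep the T2 analysis as planned. Extend the website safeguard by stating that neither the film nor its campaign goes public until the last T3 link has actually expired. Tie the hold to that event, because the two T3 rules give different dates; the stated end of November 2021 is a safe anchor. Measured from the last T2 expiry on 16 October, the wait is at most 35 days to 20 November, 38 to 23 November or 45 to 30 November, less the time the T2 analysis takes. No extra participants or data are needed.

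If release cannot wait:
- Add one T3 item asking whether the participant has seen the film or campaign outside the trial.
- Add a sensitivity analysis of the T1-to-T3 contrasts limited to participants whose latest possible T3 close falls before the release date. Compute that close from T1 date (49 days under the four-week rule, about 52 under a calendar month), so that selection does not depend on when anyone responded.

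For a 1 November release with even recruitment, the 49-day filter keeps T1 dates up to 12 September: 28/48 = 58%, or 446 × 28/48 = 260 participants. The 52-day filter keeps T1 dates up to 9 September: 25/48 = 52%, or 446 × 25/48 = 232. The fallback costs precision at T3, so holding the release is the better choice.
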